### Duration

Participants will continue on their allocated treatment arm for between 36 and 54 months. Those who have not experienced CDP by the 36-month point will be offered a further period of follow-up, if they are at a site participating in the trial extension period (see the ‘Discussion’ section). Participants in the extension period will remain on their blinded intervention for a further 6–18 months beyond the 36-month time point, dependant on the time remaining before the end of overall trial follow-up. Participants who discontinue treatment will continue to be followed up unless they withdraw consent from participation in the trial.

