### Outcomes

#### Primary outcome

The primary outcome will evaluate the effect of daily use of simvastatin (80 mg) versus placebo on disability progression at 6-monthly intervals in patients with SPMS, based on change in EDSS score compared with baseline. Progression of disability will be defined as an increase of at least 1 point if the baseline EDSS score <6, or an increase of 0.5 point if EDSS score ≥6. The initial disability progression event is finalised as positive if the disability is sustained and confirmed ≥6 months later. This allows for disability confirmation to take place if a visit is missed. This is termed CDP. The date of progression (if confirmed) will be the initial date of the progression event. EDSS is generally assessed in person, but there will be capacity for this to be collected remotely via the telephone.^46^ Time to first CDP will be compared between the simvastatin and placebo arms over treatment of up to 54 months. EDSS assessment will be performed by a blinded assessor, in line with the current version of the neurostatus scoring guidance (v04/10.2)

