## Analyses

### Statistical analysis

The primary statistical analysis will be based on all participants as randomised, irrespective of subsequent compliance with allocated treatment (intention-to-treat analysis). A secondary per-protocol analysis will be carried out including only participants who were able to comply (see the ‘Compliance’ section) with simvastatin or placebo treatment.

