### Compliance

Participants will be considered to be compliant with their randomised intervention if the summary measure of compliance is over 90%, which means they took 80 mg/2 tablets on at least 90% of days over the first 36 months of follow-up, or until the date of confirmed progression, death or withdrawal if these happened before 36 months. A secondary measure of compliance will consider participants compliant if they took either high (80 mg/2 tablets) or low (40 mg/1 tablet) dose on at least 90% of days.

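### The per-protocol set rests on compliance to month 36, but the primary outcome runs to month 54, so extension participants who stop drug but stay in follow-up are still classed as compliant

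*Protocol article*

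**What the plan says.** Under Statistical analysis, the primary analysis is "based on all participants as randomised, irrespective of subsequent compliance with allocated treatment". The same section adds: "A secondary per-protocol analysis will be carried out including only participants who were able to comply", and refers the reader to the Compliance section for the definition.

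That section counts participants as compliant if they took the full dose on 90% or more of days, counted "over the first 36 months of follow-up, or until the date of confirmed progression, death or withdrawal if these happened before 36 months". The window can therefore end early, but nothing lengthens it. A second measure is looser on dose ("A secondary measure of compliance will consider participants compliant if they took either high (80 mg/2 tablets) or low (40 mg/1 tablet) dose"), keeps the 90% threshold and gives no window of its own.

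The primary outcome has a longer horizon. Under Outcomes: "Time to first CDP will be compared between the simvastatin and placebo arms over treatment of up to 54 months". Under Duration: "Participants in the extension period will remain on their blinded intervention for a further 6–18 months beyond the 36-month time point". Duration and Withdrawal of trial participants both keep people who stop treatment in follow-up unless they withdraw consent. The censoring rule in the primary analysis section lists death, loss to follow-up, withdrawal from the trial and the last visit at which progression could be confirmed. Stopping drug is not on that list.

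**The concern.** A per-protocol analysis is read as the comparison among people who took what they were allocated. Here the label is settled at month 36, while the outcome it is applied to can accrue for a further 18 months. Intake during those months has no bearing on who is in the set.

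Take a participant who takes every tablet to month 36, enters the extension, stops drug at once and progresses at month 48. Under the rules as written, that person is compliant, is not censored on stopping, and contributes a per-protocol event a year after the last tablet. The Discussion says the extension was added to capture the number of primary events needed, so the part of follow-up that supplies the extra events is the part where compliance is not assessed.

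**Working it through.** **Inputs.** From Power and sample size: 90% power, 30% relative reduction (taken as a hazard ratio of 0.70), 5% significance, 330 events, 1050 participants, placebo progression 40% by 36 months and 49% by 54 months, loss 20% and 32%, 8% progression per 6 months. From Analysis plan: two-sided tests. From Compliance: 90% of days, first 36 months. From Duration: extension of 6 to 18 months. From the Discussion: 21 sites in the extension, of the 31 under Trial design and setting.

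**The plan's own figures.** Schoenfeld events = 4 × (1.960 + 1.282)² / (ln 0.70)² = 330.4, or 331 rounded up. Power at 330 events is 89.97%. The stated 330 reproduces. At 8% per 6 months, 1 − 0.92⁶ = 39.4% and 1 − 0.92⁸ = 48.7%, in line with the stated 40% and 49%. None of this depends on compliance.

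**How the rule classifies someone who stops at month 36.** With full intake to month 36, the score as written is 36/36 = 100%. If the first month at 40 mg is scored as not full dose, it is 35/36 = 97.2%, still above 90%. Leaving that month aside, the score over the follow-up actually analysed would be:

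| Follow-up ends | Full intake to month 36 | Exactly 90% to month 36 |
|---|---|---|
| 42 months | 36/42 = 85.7% | 32.4/42 = 77.1% |
| 48 months | 36/48 = 75.0% | 32.4/48 = 67.5% |
| 54 months | 36/54 = 66.7% | 32.4/54 = 60.0% |

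Every entry is below 90%, so the classification reverses at each extension length.

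**Events that fall outside the compliance window.**
- Placebo: (49 − 40)/49 = 18.4%.
- Simvastatin at a hazard ratio of 0.70: 1 − 0.60^0.7 = 30.1% by month 36 and 1 − 0.51^0.7 = 37.6% by month 54, so (37.6 − 30.1)/37.6 = 20.0%.
- Both arms: (9.0 + 7.5)/(49.0 + 37.6) = 19.1%.

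These shares assume that everyone eligible is followed to month 54, so they are upper figures. Adding the stated losses, and assuming that 25% to 100% of eligible people are extended, gives about 5% to 17% over both arms with eight 6-month intervals, which match the stated 49%. Counting nine intervals raises the top to about 23%, but implies 1 − 0.92⁹ = 52.8% placebo progression, more than the plan states.

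**What cannot be computed.** These are shares of all progressions after month 36. The share occurring in people who had stopped drug needs a discontinuation rate in the extension, which the article does not give.

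**The case against.** The strongest reply is that little depends on this. The primary analysis is intention-to-treat, and no interim stopping rule uses the per-protocol set. The secondary efficacy comparisons are set at or up to 36 months, as is the within-trial economic evaluation, and 36 months is the only treatment period planned for everyone. A common 36-month window is a reasonable choice for those outcomes. All of this stands.

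A second reply is that the article never says the per-protocol analysis runs to month 54, and the signed-off analysis plan, not shown here, may cut it at month 36. That is possible. But the article fixes the compliance window explicitly, gives one horizon for the primary outcome, and states no such cut. Read as written, the rule misclassifies.

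A reader might also infer several stronger things that the documents do not support:
- *That everyone who stops at month 36 counts as compliant afterwards.* People who finish at month 36 are censored and add no later time. The affected group met 90% to month 36, was free of CDP, consented to the extension at a participating site, and then stopped drug while still followed.
- *That 18% measures the bias.* It bounds the placebo events exposed to the problem. Likewise, about 546 people would be CDP-free and in follow-up at month 36 (mean CDP-free 65% × 0.80 × 1050), but that is before site participation, consent or remaining trial time.
- *That the per-protocol effect is diluted.* This requires that simvastatin works, that its benefit fades after stopping, and that stopping is unrelated to prognosis.
- *That treatment in the extension goes unchecked.* The Compliance section defines a classification. It does not say that later intake is unrecorded or unreported.
- *That the window was overlooked when the extension was added.* It matches the original 36-month design, but no earlier compliance text is shown.

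**Conclusion.** The mismatch is real and stated in the text: compliance is assessed to month 36, the primary outcome runs to month 54, and stopping drug does not censor. It affects only the secondary per-protocol analysis of the primary outcome, and within it only extension participants who stop drug while still followed. At most about 18% of placebo progressions, or 19% over both arms at a hazard ratio of 0.70, arise beyond the window. The figure is lower to the extent that eligible people did not enter the extension. The resulting bias has no computable size, and its direction is an assumption. The point is worth correcting because the analysis will be read as the effect in people who took treatment and the correction is cheap. It does not bear on the validity of the primary result.

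**What to change.** For the per-protocol analysis of the primary outcome, make the compliance window and the analysis horizon the same. There are two ways:

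1. *Simplest:* keep the 36-month window and censor the per-protocol Cox model at month 36. The wording should say whether later visits may confirm a progression first seen by month 36. The cost is the loss of later per-protocol events, at most the shares given above.
2. *Alternative:* calculate compliance from randomisation to the earliest of CDP, death, withdrawal or the last treatment-period visit, including the extension. The cost is a smaller set, the loss of up to 36 on-drug months from each person excluded, and more post-randomisation selection. For example, someone who stops at month 38 would be compliant if CDP came at month 42 (38/42 = 90.5%), but not if followed event-free to month 54 (38/54 = 70.4%), so membership would depend partly on the outcome.

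Keep the 36-month window for the 36-month outcomes. Either option takes a sentence in the plan and, for the second, a small change to the derivation. If the analysis plan already cuts the per-protocol analysis at month 36, stating that in the article is enough.

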### Interim analyses

The independent data monitoring committee (IDMC) will consider stopping for safety if there is evidence that the trial treatment is worse than placebo alone with a p<0.01 for all-cause deaths. The IDMC will consider stopping for an efficacy-based p<0.001 for a difference between the treatment groups on the primary outcome of 6 months confirmed EDSS progression. Additionally, the IDMC will consider stopping for futility based on recruitment of less than 53% of the final sample size at 15 months after starting the trial.

### Missing data

Missing data will be identified and efforts made to obtain these data. Characteristics of a total number of participants withdrawing and reasons for withdrawal will be tabulated by the treatment group and compared with those with complete data. In the event of substantial differences in withdrawal patterns being found, further sensitivity analyses will be carried out to investigate the robustness of the results.

### Analysis plan

A detailed statistical analysis plan has been written and signed off. All statistical tests will use a two-sided p value of 0.05 unless otherwise specified. Statistical analysis will be performed by using Stata v17.0 (StataCorp).

### Impact of COVID-19 on patient characteristics and trial outcomes

The impact of the COVID-19 pandemic on the trial data will be considered by comparing data collected during three periods, which were chosen based on when public health restrictions were in place in the UK:

Prior to 16 March 2020—before restrictions.From 16 March 2020 to 19 July 2021—during restrictions.After 19 July 2021—after restrictions were removed.

Baseline characteristics will be tabulated by treatment group and by mode of visit attendance (in-person vs remote) for visits occurring in the three periods identified above.

A sensitivity analysis will be performed for the primary outcome to assess the impact of COVID-19. This will compare progression at 36 months in trial participants who had EDSS collected at both baseline and month 36 in-person visits during time periods when COVID-19-related public health restrictions were not in force.

A sensitivity analysis will also be performed to compare patient-reported outcomes between trial arms using only data from visits at baseline and 36 months that were collected during periods where public health restrictions were not in force.

In addition, subgroup analyses will examine whether there is evidence that the treatment effect on the primary or secondary outcomes differed between the three time periods, by including a period of treatment interaction in the relevant model.

### Health economics analysis

A treatment that slows progression could represent a highly cost-effective use of NHS resources with the high costs of SPMS and very low cost of simvastatin. A cost–utility study will be carried out to assess the incremental cost per quality-adjusted life-year (QALY) gained from the perspective of the NHS and personal social services (PSS). Cost utility will be estimated for the ‘within trial’ period and also for the lifetime of the patient using a model-based approach.

The within-trial economic evaluation will estimate cost-effectiveness of simvastatin for the first 36 months of the trial period. Health service costs associated with SPMS include inpatient admissions (particularly during relapses or intercurrent illness), outpatient contact (including neurology consultants, MS specialist nurses and allied healthcare professionals), and GP and community care (such as physiotherapy and social worker appointments). Patient resource use will be assessed using the CSRI, a self-complete RUM and using patient records. This RUM will be modified according to the needs of people with SPMS and will be administered at baseline and 6-monthly intervals.

QALYs will be estimated, 6 monthly, using the EQ-5D-5L using the area under the curve approach. Utility scores will be calculated using UK-specific tariffs and adjusting for baseline differences in patients in the trial arms if necessary. In addition, given current uncertainties regarding the appropriateness of the EQ-5D-5L for people with SPMS,^52^ the MSIS-29v2,^53^ a condition-specific measure will be considered for estimating QALYs through methods available in the literature.^54^

The primary within-trial analysis will be intention-to-treat analysis and the secondary analysis will be per protocol analysis in line with the main statistical analysis. Results will be estimated as the incremental cost-effectiveness ratio (ICER) where data will be drawn as far as possible from the trial. Within-trial CIs for mean costs and QALYs will be calculated using a non-parametric bootstrap with replacement.^55^ The results of the non-parametric bootstrap will be presented on a cost-effectiveness plane. The bootstrap replications will be used to construct a cost-effectiveness acceptability curve, which will show the probability that the intervention is cost-effective for different values of the NHS’ willingness to pay for an additional QALY. Appropriate methods for dealing with missing trial data such as multiple imputation will be applied. We will assess the impact of COVID-19 on the ICER in the same fashion as the main statistical analysis.

The decision analytical model will take the form of a Markov model and estimate costs and benefits over the lifetime horizon of the patient to capture the progression of the condition beyond the trial period. The model will include EDSS states and a death state. A secondary analysis from a societal perspective will be undertaken which will consider additional costs borne by the patient such as time off work. Data to populate the model will be obtained from the trial and from published sources. Long-term costs and health outcomes will be discounted using discount rates recommended by the UK National Institute for Health and Care Excellence.^56^

All analyses will conform to recommended economic evaluation methods.^56^ All methods will be described in a detailed health economic analysis plan.

## Monitoring

### Oversight

A trial steering committee and independent data monitoring committee will be formally responsible for the oversight of the trial and ensuring it is conducted in compliance with Good Clinical Practice (GCP), and the relevant regulatory and ethics committee approvals.

The trial management group (TMG) will be responsible for the execution of the trial.

UCL is the sponsor for the trial, with delegated authority to the UCL Comprehensive Clinical Trials Unit (UCL CCTU).

### Safety event reporting

Site teams will report to sponsor all adverse events (irrespective of severity, causality or expectedness in relation to the trial intervention), which will take place from the time of commencement of the intervention to end of patient pathway. Adverse events meeting the ‘serious’ threshold (SAEs) will be subject to expedited reporting to sponsor (immediately and no later than 24 hours from site awareness) in line with the relevant UK regulations.

Additionally, notifiable adverse events (NAEs) for hepatotoxicity or myalgia (supported by laboratory abnormalities of ≥3 times ULN for ALT/AST, respectively) are reportable to the sponsor within the same timelines as for SAEs. Clinical review of all SAEs and NAEs will be undertaken by the sponsor, with events classified as serious adverse reactions (SARs) or suspected unexpected serious adverse reactions (SUSARs) will be onward reported in line with the relevant UK regulations and ethical approvals.

Expectedness will be determined using Section 4.8 of the approved Summary of Medicinal Product Characteristics (SmPC) for simvastatin.

Pregnancy is not an SAE, but following the initiation of the trial medication, if a female participant becomes pregnant, or female partner of a male participant becomes pregnant, then a trial pregnancy notification form will be sent to the sponsor immediately. Pregnancies will be followed up; untoward outcomes will be assessed against trial safety reporting criteria.

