**Exclusion criteria**
Relapse within 3 months of baseline visit. Patients will be eligible where 3 months from the final day of the relapse, have elapsed by the date of the baseline visit.Patients who have been treated with steroids (intravenous and/or oral) due to MS relapse/progression within 3 months from the final day of relapse to the baseline visit. These patients may undergo a further screening visit once the 3-month window has expired and may be included if no steroid treatment has been administered in the intervening period.(Patients on steroids for another medical condition may be included in the trial provided the steroid prescription is not for MS relapse/progression).Significant organ comorbidity, for example, cardiac failure, renal failure, malignancy.Screening levels of alanine aminotransferase/aspartate aminotransferase or creatine kinase ≥3×upper limit of normal.Current use of a statin; or any use within the last 6 months.Medications that interact unfavourably with simvastatin as outlined in the current summary of product characteristics (Summary of Medicinal Product Characteristics); including but not limited to CYP3A4 inhibitors (eg, itraconazole, ketoconazole, posaconazole, voriconazole, fluconazole, HIV protease inhibitors (eg, nelfinavir), boceprevir, erythromycin, clrithromycin, telithromycin, telaprevir, nefazodone, fibrates (including fenofibrates), nicotinic acid (or products containing niacin), azole antifungal preparations, macrolide antibiotics, protease inhibitors, verapamil, amiodarone, amlodipine, gemfibrozil, ciclosporin, danazol, diltiazem, rifampicin, fusidic acid, elbasvir, grazoprevir, ticagrelor, daptomycin, grapefruit juice or alcohol abuse.Primary progressive MS.Diabetes mellitus type 1.Uncontrolled hypothyroidism.Female participants who are pregnant or breast feeding. Women of childbearing potential who are unwilling or unable to use an acceptable method to avoid pregnancy for the entire study period, and up to 4 weeks after the last dose of study drug.Use of immunosuppressants (eg, azathioprine, methotrexate, ciclosporine) or disease-modifying therapies (avonex, rebif, betaferon, glatiramer) within the previous 6 months.Use of mitoxantrone, natalizumab, alemtuzumab, daclizumab or other monoclonal antibody treatment, if treated within the last 12 months.Use of fingolimod, dimethyl fumarate, teriflunomide, cladribine within the last 12 months.Use of other experimental disease-modifying therapy within the last 6 months.Commencement of fampridine ≤6 months from the day of randomisation.Concurrent participation in another clinical trial of an investigational medicinal product or medical device.Patients with rare hereditary problems of galactose intolerance, the Lapp lactase deficiency or glucose-galactose malabsorption.

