### Dose modification and stopping

The dose may be varied for patients experiencing hepatic effects, myopathy/rhabdomyolysis or other adverse events at the principal investigator’s discretion. Where elevated alanine aminotransferase (ALT), aspartate aminotransferase (AST) or creatine kinase (CK) levels are sustained at ≥3×upper limit of normal (ULN), it is recommended that the dose is lowered (from 80 mg (active/placebo) to 40 mg (active/placebo)), with rechallenge at the higher dose possible after parameters return to normal. For ALT, AST or CK levels ≥5×ULN, trial medication should be stopped, with rechallenge only permissible where the intervention was clearly determined to be non-causally related (eg, another intercurrent medication or infection, which has now resolved, produced the biochemical abnormalities).

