### Secondary outcomes

The proportions of participants with confirmed progression at 36 months on the composite (multicomponent) disability progression outcome (EDSS, T25FW or 9HPT), and proportions with confirmed progression on the individual outcomes making this composite, will be compared between arms using logistic regression adjusting for the minimisation variables as fixed effects. Proportions with progression on mRS at 36 months will also be compared using logistic regression, adjusting for the minimisation variables. ORs and 95% CIs will be presented along with the p value for a Wald test for the difference between treatment groups.

Baseline to 36 months change in continuous clinician and patient-reported outcomes will be compared between groups using linear mixed models for repeated measures. For each outcome, the difference in mean of the outcome at 36 months will be reported alongside 95% CIs and the two-sided p value. Analysis of MSIS-29v2, MSWS-12v2, MSFIS-21 and CFQ will use data recorded at all available visits. Analysis of MSFC, T25FW, 9HPT, SLCVA, CVLT-II, BVMT-R and SDMT will use data recorded at baseline and 36 months (due to COVID-19 as described below). The dependent variable will be the outcome at each time point. Treatment group will be included as predictor, with treatment by visit interaction, but at baseline the treatment effects will be constrained to be zero, which is essentially equivalent to adjusting for baseline using analysis of covariance (ANCOVA).^51^ An unstructured covariance matrix for the residuals will be used to allow for correlation between repeated measures on an individual. The minimisation variables, and their interactions with visit, will be included as fixed effects. If parametric assumptions for the linear regression model are substantially violated, bias-corrected and accelerated bootstrap confidence intervals will be used for inference.

The relapse rate up to 36 months will be compared between groups using negative binomial regression adjusting for the minimisation variables as fixed effects. Numbers of relapses by grade, adverse events, serious adverse events and notifiable adverse events will be tabulated by treatment group.

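### The notifiable-event definition gives myalgia no creatine kinase criterion, so a non-serious muscle event that stops the drug on CK need not be notifiable

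*Protocol article*

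**What the plan says.** Under Monitoring, Safety event reporting, the protocol article creates a class of notifiable adverse events for "hepatotoxicity or myalgia (supported by laboratory abnormalities of ≥3 times ULN for ALT/AST, respectively"). These go to the sponsor on the same clock as serious adverse events (SAEs), which is at most 24 hours after the site learns of the event. The same section states "Clinical review of all SAEs and NAEs will be undertaken by the sponsor". It also sets the general duty: "Site teams will report to sponsor all adverse events (irrespective of severity, causality or expectedness in relation to the trial intervention").

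Under Analyses, Secondary outcomes: "Numbers of relapses by grade, adverse events, serious adverse events and notifiable adverse events will be tabulated by treatment group".

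Two other sections use CK:

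- **Dose modification and stopping** names muscle toxicity beside liver toxicity: "The dose may be varied for patients experiencing hepatic effects, myopathy/rhabdomyolysis or other adverse events". A lower dose is recommended where alanine aminotransferase, "aspartate aminotransferase (AST) or creatine kinase (CK) levels are sustained at ≥3×upper limit of normal (ULN"). Then: "For ALT, AST or CK levels ≥5×ULN, trial medication should be stopped".
- **Exclusion criteria (Box 1)** exclude on "Screening levels of alanine aminotransferase/aspartate aminotransferase or creatine kinase ≥3×upper limit of normal".

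**The concern.** The NAE rule names two events, one of the liver and one of muscle, and then lists markers that are meant to match them in order. Only ALT and AST appear. The muscle event is left either with AST alone or with the same transaminases as the liver event. On neither reading does it have CK, the marker that the article itself adds to the transaminases when it sets eligibility and dosing.

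NAE status carries three things: the 24-hour route, a stated clinical review by the sponsor, and a separate line in the safety table by arm. A non-serious muscle event supported by CK alone would have none of them. The active arm is assigned 80 mg daily for 36 to 54 months after a first month at 40 mg, and the rule plainly sets out to capture muscle events. A reader of the NAE table cannot tell from the article whether CK-supported myalgia was counted.

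**Working it through.** The protocol states no figure to reproduce, so the check is one of logic, followed by an illustration of size.

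**1. The rules side by side**

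| Section | Purpose | Markers | Threshold |
|---|---|---|---|
| Exclusion criteria | eligibility | ALT/AST, CK | ≥3×ULN |
| Dose modification and stopping | dose reduction recommended | ALT, AST, CK | sustained ≥3×ULN |
| Dose modification and stopping | stop trial medication | ALT, AST, CK | ≥5×ULN |
| Safety event reporting | NAE notification | ALT, AST | ≥3×ULN |

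Three rules use three markers. The notification rule uses two, although it names a muscle event and shares the 3×ULN threshold. The first three rows govern eligibility and dosing, not notification. They therefore do not contradict the fourth row directly, but they do show it to be out of line.

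**2. A test case**

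Take a non-serious myalgia with CK ≥5×ULN and with ALT and AST both <3×ULN.

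- Dose modification and stopping: CK is ≥5×ULN, so trial medication should be stopped.
- NAE rule, reading (a), ALT paired with hepatotoxicity and AST with myalgia: AST is <3×ULN, so the event is not an NAE.
- NAE rule, reading (b), either transaminase for either event: both are <3×ULN, so the event is not an NAE.
- NAE rule with CK supplied for myalgia: CK is ≥3×ULN, so the event is an NAE.

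Both literal readings give the same result, and adding CK reverses it.

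**3. What the event loses and keeps**

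- Lost: the 24-hour route, the sponsor review stated for SAEs and NAEs, and a place in the NAE count by arm.
- Kept: reporting to the sponsor as an adverse event, a place in the adverse event table by arm, and the dose rules.
- Not affected: events that meet the serious criteria (expedited anyway), and muscle events that also raise the relevant transaminase to ≥3×ULN. That means AST under reading (a), and either ALT or AST under reading (b).

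**4. Illustration of size**

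The article gives 525 participants per arm (Power and sample size) and no rate of CK-only myalgia. The rates below are assumptions, with one event per affected participant.

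Events outside the definition in an arm = assumed proportion × 525

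- 0.2%: 0.002 × 525 = 1.05, about 1
- 1%: 0.01 × 525 = 5.25, about 5
- 2%: 0.02 × 525 = 10.5, 10 or 11

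The definition applies to both blinded arms alike, so both NAE counts could be low. The between-arm NAE difference shrinks only if such events are more frequent in one arm.

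**The case against.** The strongest reply is that this is an editorial slip in a condensed article. The article is based on protocol v8.0, and nothing suggests that sites report from the article. If v8.0 and the NAE form name CK, reporting was never affected. That stands, and it limits what can be concluded: the printed wording is shown to be wrong, but a gap in actual reporting is not. It does not remove the error. The article states the rule in full, with events, markers and threshold, so this is not detail left to a fuller document.

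A second reply is that pairing AST with myalgia could be deliberate, as a narrow subset for expedited reporting, since no section requires CK for notification. The text cannot exclude this. It is the less likely reading, because the article uses CK in each of its other laboratory rules, and it still leaves the test case outside the definition.

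A third reply is that participants are protected by the dose rules whatever the NAE status, and that non-serious adverse events still reach the sponsor and may be seen in central data review. This stands. The article does not say that ordinary adverse events go unreviewed. It promises clinical review only for SAEs and NAEs.

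Finally, the trial was due to conclude in August 2024 and v8.0 is dated February 2024, so a text change would do little for 24-hour notification. That also stands. What can still be protected is the NAE table and how it is read.

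**Conclusion.** The concern holds: the NAE definition is wrong as written. On either literal reading, a non-serious myalgia supported by CK alone is not notifiable, even when the same CK value means the drug should be stopped.

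The consequence is confined to expedited notification, the stated sponsor review and the NAE count for one type of muscle event. Under the assumed rates that is about 1 to 11 events in an arm, all of which remain in the adverse event table. The primary analysis, power, type I error and interim stopping guidelines do not depend on this definition.

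That the article's wording is defective is clear. Whether trial conduct was affected depends on protocol v8.0 and the NAE form, neither of which is shown, so overall confidence is medium. The point should be fixed because it concerns an operative safety rule and costs almost nothing to correct.

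**What to change.** Restate the definition so that each event has its own marker: hepatotoxicity supported by ALT or AST ≥3×ULN, and myalgia supported by CK ≥3×ULN. In the existing sentence this means inserting *or CK* after the transaminases, which gives *respectively* something to refer to.

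Then confirm that protocol v8.0 and the NAE reporting form say the same. Only if they share the omission, list the CK results and muscle adverse events already collected, check them against the corrected definition before NAEs are tabulated, and state in the report that this was done.

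The cost is two added words and a check of two documents. The listing is extra work only in the conditional case, and it uses data already held.
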